### Statistical analysis methods

The data obtained will be analyzed using SPSS Statistics version 18 (IBM Corp) software and evaluated using comparative and descriptive statistics. Student *t*-test will be used for normally distributed parametric data, while Mann-Whitney U-test will be used for non-normally distributed data. The χ^2^ test and Fisher exact test will be used to evaluate categorical data. A correlation between data will be evaluated using Pearson correlation coefficients for parametric data and Spearman correlation coefficients for non-parametric data. Descriptive statistics will be presented as median (range), mean ± SD, or number/frequency (percentage). Statistics will be considered significant when the *P*-value < 0.05.

#### Handling of predictors

The collected data will first be preprocessed, including data cleansing, outlier processing, and data transformation. Data cleaning is the process of deleting redundant information and correcting information with obvious errors. Based on the data situation, we will choose between deletion, imputation, or substitution for outlier processing. The data will be transformed in the following ways: continuous variables will be kept in the model as continuous variables if they are linear or will be combined with similar segments if they are non-linear (treated as binary categories or ordered categories); ordered multicategorical variables will be treated as rank variables or dummy variables as appropriate, and when not linearly related to the outcome, optimal scale regression will be used to explore effect inflection points; unordered multicategorical variables need to be split into multiple binary variables (Figure 2).

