**Individual susceptibility factors**			
Age	Adolescent's age	Continuous & Categorical	Years (age classified into approximately three to four categories)
Nationality	Adolescent's nationality	Binary	0 “the Han nationality” 1 “minority nationality”
Body mass index(BMI)	Body mass divided by the square of the body height	Continuous	kg/m^2^
Waist-to-hip ratio (WHR)	WHR is found by dividing circumference of the waist by the circumference of the hips	Continuous	
Living residence	Current residence of adolescents	Binary	0 “City” 1 “Countryside”
Education level	Current educational level of adolescents	Categorical	Education level classified into approximately five categories
Single parent family	Adolescents live with only one parent	Binary	0 “No” 1 “Yes”
Family history of mental illness	Mental illness within three generations in the paternal, maternal, direct and collateral lines in adolescents	Binary	0 “No” 1 “Yes”
Duration of illness	Time since first diagnosis of PCOS	Categorical	Duration of illness classified into approximately five to six categories
Personality	Eysenck Personality Questionnaire-Junior (42)	Continuous	
Emotional regulation skills	Emotion Regulation Scale (43)	Continuous	

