**Figure 2 F2:**
[figure not shown]
Simulation diagram for developing and validating a LASSO-based model to predict depression in adolescents with PCOS.

Preprocessed data will be assigned variable values according to various variable types and a data set in CSV format will then be generated.

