#### Model-building procedures (including predictor selection)

After the data set is imported into the R software, it will be divided into 80% training data and 20% validation data. The training data will be used to build the warning model, and the validation data will be used for internal validation.

To begin with, we will use R software to read the features of the dataset. After that, we will load the two R packages “corrplot” and “glmnet.” By using the cor() function, we will create a correlation object “corrlate” and visualize the correlation coefficient. The predictors and outcome variables in the training and validation sets will be encoded into matrices, the predictors will be stored in X vectors, and the outcome variables in Y vectors. A LASSO regression will be performed when alpha is set to one. The program will then be run. When the parameter lambda is greater, the estimated parameters will also be compressed to a smaller degree. As lambda reaches a certain value, some variables that are not important to the model will be compressed to zero, indicating that these variables will be eliminated. Thus, the lambda corresponding to the optimal result, the influencing factors of preliminary screening, and the regression coefficient will be obtained.

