#### Internal validation and assessment of model performance

Internal validation will be conducted using the 20% validation set samples and will utilize a cross-validation method based on 10 folds. Then, the result of LASSO cross-validation will be obtained, and the lambda when it is one standard error away from the mean square error will be considered optimal (at this time, the mean square error is small, and the number of independent variables is also small). For that lambda case, we will examine the regression coefficients and exclude variables with a regression coefficient of zero. Those variables with regression coefficients other than zero are selected, thereby identifying the influencing factors that are significantly associated with depression in PCOS adolescents. After screening the variables, a multivariate linear model will be constructed.

The prediction accuracy of the model will be reflected by discrimination and calibration. In this study, the C-statistic is used to measure discrimination, followed by a calibration plot to measure the accuracy of the absolute risk predictions of the warning model. An evaluation of the fit will be performed by drawing a scatter plot.

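### Non-linear continuous predictors are to be categorised, and the recoding comes before the 80/20 split, so information is lost and any outcome-guided recoding makes internal validation optimistic

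*Protocol article*

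**What the plan says.** All references are to the protocol article.

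- **Rule for continuous predictors** (Handling of predictors): "continuous variables will be kept in the model as continuous variables if they are linear"; otherwise they "will be combined with similar segments if they are non-linear (treated as binary categories or ordered categories". No option that keeps a non-linear predictor continuous is offered.
- **Rule for ordered multicategorical predictors** (same sentence, next clause): they enter as ranks or dummies, and "when not linearly related to the outcome, optimal scale regression will be used to explore effect inflection points".
- **Order of steps.** Handling of predictors opens with "The collected data will first be preprocessed, including data cleansing, outlier processing, and data transformation". It ends, after Figure 2, with "Preprocessed data will be assigned variable values according to various variable types and a data set in CSV format will then be generated". Model-building procedures then begins: "After the data set is imported into the R software, it will be divided into 80% training data and 20% validation data".
- **Use of the 20%** (Internal validation and assessment of model performance): "Internal validation will be conducted using the 20% validation set samples". Ten-fold cross-validation chooses lambda.
- **Table 1** types 22 predictors as continuous: 11 body measures and scale scores, and 11 laboratory values. Age is both continuous and categorical. Illness duration is categorical ("Duration of illness classified into approximately five to six categories"), as is duration of medicine use.

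**The concern.** There are two separate problems.

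**Loss of information.** A hormone level, BMI or scale score reduced to two or a few groups makes everyone within a group equal and makes predicted risk jump at the boundaries. The loss is worst for the predictors that the rule targets: a single cut cannot represent a risk that rises at both ends of a range.

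**Leakage.** If segments are merged, or inflection points chosen, by looking at depression status, that recoding is part of model fitting. Done on the whole development file before the split, it carries validation outcomes into the predictors. The internal C-statistic and calibration plot then flatter the model. The folds that choose lambda are no longer clean either, so noise variables recoded to fit the outcome are more likely to be kept. The protocol's second aim is to establish the accuracy and validity of the model, so this bears directly on a stated objective.

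**Working it through.** **1. The plan's own figure.** Sample size and calculation: n = (1.96/0.05)² × 0.4 × 0.6 = 368.8, rounded up to 369. It reproduces. The point does not depend on it.

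**2. Numbers available.** The section expects 800 PCOS participants over 12 months and an outcome proportion of 0.4. Assuming even accrual and PCOS participants only:
- January to August: 800 × 8/12 = 533
- training: 0.8 × 533 = about 427
- internal validation: 0.2 × 533 = about 107
- training events: 0.4 × 427 = about 171

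**3. Loss for a non-linear effect.** Assume a standard normal predictor X with logit(risk) = −0.994 + 0.607·X², which gives 40% prevalence and a full-shape C of 0.670. Each group has its own fitted risk.

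| Form of X | C |
|---|---|
| Continuous, true shape | 0.670 |
| Best single cut | 0.566 |
| Four equal groups | about 0.62 |
| Five equal groups | 0.635 |

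The loss is about 0.10 with one cut, 0.05 with four groups and 0.035 with five. For a saturating effect with full-shape C of 0.684, one cut gave 0.637 to 0.656 and five groups gave 0.675 to 0.679.

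**4. Loss if a linear predictor is wrongly judged non-linear.** The share of a normal predictor's information kept by k equal groups is Σ Pₖmₖ², where Pₖ is the proportion in the group and mₖ its mean. It is 64% for two groups, 79% for three, 86% for four and 90% for five.

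**5. Leakage.** The simulation used 533 records, an 80/20 split, 200 replicates, independent normal predictors and a ridge-penalised logistic model fitted on the training part. Every predictor was dichotomised at its outcome-optimal cut, found either on all 533 records or on the training part only. Where there is signal, three predictors have U-shaped effects. New data means fresh records from the same model.

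| Predictors | Signal | Cuts from all data: 20% set / new data | Cuts from training only: 20% set / new data | Continuous with quadratic term: 20% set / new data |
|---|---|---|---|---|
| 10 | none | 0.595 / 0.501 | 0.496 / 0.501 | 0.499 / 0.501 |
| 10 | three | 0.648 / 0.572 | 0.566 / 0.571 | 0.675 / 0.675 |
| 22 | none | 0.636 / 0.499 | 0.495 / 0.499 | 0.500 / 0.499 |
| 22 | three | 0.686 / 0.555 | 0.556 / 0.554 | 0.654 / 0.652 |

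Optimism with cuts from all data is 0.595 − 0.501 = 0.094, then 0.076, 0.137 and 0.131 down the rows. With training-only cuts, the 20% set and new data agree within 0.006.

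With fewer recoded predictors (unpenalised logistic model, pure noise, 500 runs), whole-file cuts gave a C in the 20% set of 0.575 for three predictors and 0.615 for ten. Training-only cuts gave 0.503 and 0.498. The bias shrinks with fewer recoded predictors but does not vanish.

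**The case against.** The strongest reply is about what the text actually says.

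- **Use of the outcome.** A reader might infer that the plan states an outcome-based search for cut-points in continuous predictors. It does not. The clause on inflection points follows a semicolon and governs ordered multicategorical variables only. For continuous predictors, use of the outcome is an inference. It is a strong one, because linearity in a prediction model, and which segments count as similar, can hardly be judged except against the outcome.
- **Which records inform the recoding.** The text does not name them, and Figure 2 is not available. Even so, the stated sequence is transform, write the file, import, split, and nothing confines the recoding to training data.
- **Temporal validation.** A reader might infer that this is contaminated too. The text does not say whether the September to December data are preprocessed with the rest, so that check may be clean.
- **Table 1.** Age is not simply categorised, since a continuous form is listed as well. The durations are not shown to be recorded continuously; they may be questionnaire bands, and nothing says that the bands come from the outcome.
- **Size.** The single-cut figures are the extreme option, because the plan also allows ordered categories. A noise predictor cut at its best point reaches p < 0.05 in about 45% of simulated data sets of 533, but that does not describe this plan, which selects by LASSO and not by p-value.

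These limits stand. They narrow the point without removing the planned categorisation or the order of steps.

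**Conclusion.** The concern holds in two parts.

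**Categorisation** of non-linear continuous predictors is stated and costs discrimination. The cost is large for a single cut through a U-shaped effect (C of 0.67 to 0.57) and smaller with four or five groups (about 0.62 to 0.635). These values rest on assumed shapes and a normal predictor.

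**Leakage** follows from the stated order wherever the outcome guides the recoding. That is explicit for ordered multicategorical variables and very probable for continuous ones. The internal C-statistic and calibration would then be optimistic. The simulated 0.08 to 0.14 assumes that 10 or 22 predictors are all dichotomised at their best cut, with a ridge penalty in place of LASSO; the actual size depends on how many are recoded and into how many groups. The effects on calibration and on the choice of lambda follow by reasoning and were not simulated.

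The documents do not support a claim that the temporal validation is biased. A clean temporal cohort would expose the optimism, but it would not restore the lost information.

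**What to change.** **Handling of predictors.** Replace categorisation of non-linear continuous predictors with pre-specified flexible continuous terms, for example restricted cubic splines with knots at fixed percentiles. Limit these to predictors where non-linearity is plausible beforehand: one or two extra terms for each of 22 predictors would add 22 to 44 terms against about 171 training events. Use both durations as continuous where raw values are recorded. Keeping or dropping the terms of one variable together (group LASSO) is an option, not a requirement.

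**Handling of predictors and Model-building procedures.** Move the split ahead of any outcome-dependent recoding. Derive such recoding, including the optimal scale step, in the training data only, and repeat it within each cross-validation fold. Apply the resulting transformation unchanged to the 20% set and to the September to December cohort, and state that the later cohort plays no part in deriving it.

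**Cost.** Plan wording and a little more analysis, with no extra participants. The model gains a few terms and the nomogram axes become slightly less simple.

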**Figure 2 F2:**
[figure not shown]
Simulation diagram for developing and validating a LASSO-based model to predict depression in adolescents with PCOS.

Preprocessed data will be assigned variable values according to various variable types and a data set in CSV format will then be generated.

#### Model-building procedures (including predictor selection)

After the data set is imported into the R software, it will be divided into 80% training data and 20% validation data. The training data will be used to build the warning model, and the validation data will be used for internal validation.

To begin with, we will use R software to read the features of the dataset. After that, we will load the two R packages “corrplot” and “glmnet.” By using the cor() function, we will create a correlation object “corrlate” and visualize the correlation coefficient. The predictors and outcome variables in the training and validation sets will be encoded into matrices, the predictors will be stored in X vectors, and the outcome variables in Y vectors. A LASSO regression will be performed when alpha is set to one. The program will then be run. When the parameter lambda is greater, the estimated parameters will also be compressed to a smaller degree. As lambda reaches a certain value, some variables that are not important to the model will be compressed to zero, indicating that these variables will be eliminated. Thus, the lambda corresponding to the optimal result, the influencing factors of preliminary screening, and the regression coefficient will be obtained.

#### Internal validation and assessment of model performance

Internal validation will be conducted using the 20% validation set samples and will utilize a cross-validation method based on 10 folds. Then, the result of LASSO cross-validation will be obtained, and the lambda when it is one standard error away from the mean square error will be considered optimal (at this time, the mean square error is small, and the number of independent variables is also small). For that lambda case, we will examine the regression coefficients and exclude variables with a regression coefficient of zero. Those variables with regression coefficients other than zero are selected, thereby identifying the influencing factors that are significantly associated with depression in PCOS adolescents. After screening the variables, a multivariate linear model will be constructed.

The prediction accuracy of the model will be reflected by discrimination and calibration. In this study, the C-statistic is used to measure discrimination, followed by a calibration plot to measure the accuracy of the absolute risk predictions of the warning model. An evaluation of the fit will be performed by drawing a scatter plot.

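### The model-building and internal-validation sections conflict on which data tune lambda and select predictors; as written, the 20% set is not an independent check

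*Protocol article*

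**What the plan says.** All of this is in the protocol article.

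- **Model-building procedures (including predictor selection).** The development data set is split: "it will be divided into 80% training data and 20% validation data". Roles are then assigned: "The training data will be used to build the warning model, and the validation data will be used for internal validation". The section ends with "Thus, the lambda corresponding to the optimal result, the influencing factors of preliminary screening, and the regression coefficient will be obtained", a first result from the LASSO for which no criterion is given.
- **Internal validation and assessment of model performance.** The section opens with "Internal validation will be conducted using the 20% validation set samples and will utilize a cross-validation method based on 10 folds". From that cross-validation, "the lambda when it is one standard error away from the mean square error will be considered optimal". Then "For that lambda case, we will examine the regression coefficients and exclude variables with a regression coefficient of zero", and "Those variables with regression coefficients other than zero are selected". It continues: "After screening the variables, a multivariate linear model will be constructed". The C-statistic and calibration plot come after this, with no data set named for them.
- **External validation.** The September to December 2022 patients form a temporal validation cohort. Risk scores are to be calculated there, and the model is also to be refitted there.

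**The concern.** A hold-out set measures overfitting only if nothing about the model was decided with it. Choosing the penalty and choosing the predictors are the two decisions through which a LASSO model overfits. If both are made by cross-validation inside the 20% set, the model has already been adapted to those patients, and its discrimination and calibration in them will tend to look better than in new patients.

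There is a second consequence. The 20% set is the smaller part of the data, so the predictor list would rest on a fraction of the available events while the larger part plays no stated role in the choice.

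Validating the model's accuracy is one of the two stated aims, and the model is to be presented as a nomogram for clinical staff. The internal performance figures therefore matter to the reader of the results.

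**Working it through.** **1. The plan's own figure.** The sample-size section uses n = (1.96/δ)² × φ(1 − φ) with φ = 0.4 and δ = 0.05. This gives (1.96/0.05)² × 0.24 = 368.79, rounded up to 369, as stated. The figure is not in dispute. It concerns the precision of a proportion and does not bear on which data tune the model.

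**2. Which data each step uses.**

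| Step | Model-building section | Internal-validation section |
|---|---|---|
| Build the model | 80% | – |
| Internal validation | 20% | 20% |
| 10-fold cross-validation | not mentioned | 20% |
| Choice of lambda | an optimal value is obtained, no criterion | one-standard-error value from that cross-validation |
| Choice of predictors | a preliminary screening | non-zero coefficients at that lambda |
| Multivariate model after screening | – | data not named |
| C-statistic, calibration | – | data not named |

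The two sections each claim to yield a lambda and a set of variables. The only data set named alongside the cross-validation is the 20%. No sentence places the cross-validation in the 80%, and none says that a fixed model is scored in an untouched 20%.

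**3. Size of the 20% set.** The inputs are 800 PCOS patients over January to December 2022 and 400 controls (sample-size section), 80 to 100 patients a month (Participants), a development window of January to August, i.e. 8 of 12 months (Patient recruitment), and an outcome proportion of 0.4 (sample-size section). Table 1 lists 31 candidate rows before dummy coding.

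| Assumption | Development N | 80% | 20% | Events in 20% (×0.4) | Events per candidate row, 20% | Same, 80% |
|---|---|---|---|---|---|---|
| 800 accrue evenly: 800 × 8/12 | 533 | 427 | 107 | 43 | 1.4 | 5.5 |
| 80 a month × 8 | 640 | 512 | 128 | 51 | 1.7 | 6.6 |
| 100 a month × 8 | 800 | 640 | 160 | 64 | 2.1 | 8.3 |
| 533 + all 400 controls | 933 | 747 | 187 | 75 | 2.4 | 9.6 |

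Even accrual is an assumption. The last row assumes that every control enters the development data and that 0.4 applies to controls too; the article states neither, so 75 events is an upper figure. With 107 patients, each of ten folds holds about 11 patients and 4 events.

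**4. Direction of the bias.** An illustrative simulation used 200 runs, 427 training and 107 validation patients, 31 independent normal predictors, of which 6 had a log-odds ratio of 0.35 per SD, and a linear LASSO with 10-fold cross-validation and the one-standard-error rule. The effect sizes and the independence of the predictors are assumptions. A run that selected nothing counts as C = 0.5.

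| Procedure | Mean C in the 107 | Mean C in new data | Difference |
|---|---|---|---|
| Select and fit in the 107 | 0.622 | 0.548 | 0.07 |
| Select in the 107, fit in the 427 | 0.598 | 0.554 | 0.04 |
| Select and fit in the 427 | 0.681 | 0.679 | 0.00 |

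Selection in the 107 returned no predictor in 58% of runs (proportion 0.585). The second row matters most for this plan: even if the last fit uses the training data, selecting in the 20% is enough to make the 20% optimistic in this setting. When no predictor had any effect, that same procedure showed no optimism (0.495 against 0.500), so the amount depends on the assumed effects.

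**The case against.** The strongest reply is that this is loose drafting. The model-building section says plainly that the training data build the model, and it already places an optimal lambda and a screening step there. On that reading the cross-validation belongs to the training fit, the 20% is an ordinary hold-out, and one clarifying sentence settles the matter. The development and validation diagram (Figure 2) is not available in the text reviewed and cannot be checked. This reading may well be what was intended. It does not remove the finding, because the internal-validation section says otherwise and an analyst following it would tune in the 20%.

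A reader might infer that the final model is certainly fitted in the 20%, or that the study has no independent validation at all. The documents do not support either. The data for the multivariate fit are not named, and the September to December cohort is separate data in which risk scores are to be calculated. That cohort is only a partial answer, because a model refitted there is no longer the developed model under test.

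A reader might also infer a specific, large optimism. That would go beyond the text: any such number rests on assumed effects, and a set of 107 is only the lowest of several plausible sizes.

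Finally, it can be said that a single 80/20 split is inefficient. At C = 0.75 the Hanley–McNeil 95% half-width is about 0.098 with 107 patients and 0.089, 0.080 and 0.074 with 128, 160 and 187. This shows limited precision, but it is a matter of preference and not an error in the plan.

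**Conclusion.** The concern holds as a contradiction between two sections that must be resolved before analysis. The 20% set is declared for validation, yet it is the set named for the cross-validation that fixes lambda and the predictors. Selection alone breaks independence, so the conclusion does not depend on where the last model is fitted.

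If the internal-validation section is followed, predictors are chosen from roughly 107 to 160 PCOS patients (43 to 64 events at 0.4), or up to about 187 participants with all controls, and the internal C-statistic and calibration will tend to be too favourable. The lower end assumes even accrual of 800; 128 to 160 follows from the stated clinic volume. The simulated differences of 0.04 to 0.07 in C show direction only. If the authors meant to tune in the training data, the harm disappears once the text says so. The temporal cohort, with its stated refit, does not clearly repair the gap.

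**What to change.** State in both sections that the 10-fold cross-validation, the choice of lambda, the selection of variables and the final fit all use the 80% training data only. State that the resulting model, with coefficients frozen, is then scored once in the 20%, and that the internal C-statistic and calibration plot come from that scoring. Remove the wording that places the cross-validation in the 20% set, and say how the preliminary screening relates to the one-standard-error choice.

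As an option, not needed to cure the contradiction, use all January to August data for development, with lambda tuned by cross-validation inside it. Then report an optimism-corrected C-statistic and calibration slope from a bootstrap that repeats every step (recoding of predictors, lambda choice, selection, refit) in each resample.

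The cost is wording and computing time. No further patients or data are needed. The internal performance figures may come out lower than under the procedure as written.

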
**Figure 1 F1:**
[figure not shown]
Simulation map of risk factors for depression in adolescents with PCOS.

As previously noted, the occurrence of depression in adolescents with PCOS involves multiple dimensions and contains numerous independent variables. To minimize the bias caused by the absence of important independent variables, it's important to select as many variables as possible at the beginning of the warning model construction process. Traditional regression analysis methods using statistical software such as SPSS, Jamovi, etc., can quantitatively analyze the strength of a predictor based on the regression coefficient. However, conventional regression analysis methods cannot handle collinearity problems and produce high variance when there are numerous independent variables. Least Absolute Shrinkage and Selection Operator (LASSO) is a type of machine learning method introduced by Tibshiran in 1996 (26). On the one hand, LASSO can select features automatically. When there are numerous independent variables, LASSO can selectively integrate powerful explanatory factors into the model. On the other hand, LASSO can compress the coefficients of some minor or insignificant independent variables to zero and pick more relevant independent variables to prevent overfitting. As compared to traditional regression analysis methods, LASSO can process all independent variables simultaneously, which greatly increases the model's stability. LASSO has been gradually applied to the development of warning models in the medical area in recent years (27, 28), as it offers high stability, fast calculation speed, and ease of interpretation in building warning models. To date, LASSO has been applied to the construction of diagnostic prediction models, early risk identification of ischemic stroke, for example (27). LASSO has also been applied to the construction of prognostic prediction models, for instance, survival after ampullary adenocarcinoma resection (28). Additionally, a study based on LASSO used electronic primary care data to develop a predictive model of common mental disorders among adolescents and early adults (29). But the study noted that primary care data underestimated common mental disorders. Due to race and PCOS, the model cannot predict depression with PCOS in adolescents. Thus, we will explore the causes of depression in teenagers with PCOS and the influence of a variety of risk variables, as well as develop and test a depression risk prediction model for adolescents with PCOS. Not only will this model be able to identify high-risk groups for depression with PCOS in adolescence, but also for high-risk groups of depression in general adolescent girls.

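### The one-SE lambda from a single described 10-fold cross-validation decides the factor list, so the list could change when only the random folds are redrawn

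*Protocol article*

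**What the plan says.** Under 'Model-building procedures (including predictor selection)', the Protocol article splits the development data 80/20, loads glmnet, sets alpha to one and continues: "The program will then be run". The variables left at the optimal lambda are the result.

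The next section, 'Internal validation and assessment of model performance', supplies the tuning rule. The procedure "will utilize a cross-validation method based on 10 folds", and "the lambda when it is one standard error away from the mean square error will be considered optimal". What follows depends on that one value: "Those variables with regression coefficients other than zero are selected", "thereby identifying the influencing factors that are significantly associated with depression in PCOS adolescents". The risk model is then built on the same list: "After screening the variables, a multivariate linear model will be constructed". A nomogram is the intended presentation ('External validation').

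The text gives the number of folds and the rule for lambda. It does not mention repeated partitions, a seed, or any check of how stable the selection is.

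**The concern.** Ten-fold cross-validation assigns girls to folds at random. The minimum of the error curve and its standard error both depend on that assignment, so the one-SE lambda does too. In many applications a small shift in lambda hardly matters. Here lambda alone decides which variables enter the model and are reported as influencing factors. The Discussion lists the identification of those factors as the first of the study's three questions.

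If the list moves with the folds, the same analyst running the same code on the same girls could report a somewhat different set of factors and a different risk score. A reader of the final article would have no means of seeing this.

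**Working it through.** **The plan's own figure.** 'Sample size and calculation' gives n = (1.96/0.05)² × 0.4 × 0.6 = 1536.64 × 0.24 = 368.79, rounded up to 369. This reproduces. It sets the precision of the overall depression proportion and says nothing about the stability of variable selection.

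**Sample sizes.** The article expects 800 PCOS patients in 12 months, with January to August for development. With even accrual (assumption), 800 × 8/12 = 533. The 80% training part is 427 and the 20% validation part is 107. At the upper clinic rate in 'Participants', 100 × 8 × 0.8 = 640.

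**Columns.** Table 1 has 31 candidate rows. About 48 columns after dummy coding and subscales is an assumption.

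**Assumed data.** 40% depressed (the article's 0.4), common correlation 0.3, and 12 true predictors: five with log-odds 0.45 and seven with 0.2 per SD, or half of these. None of the effects or correlations comes from the documents.

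**Method.** LASSO with squared-error loss, because the article tunes on mean square error. The chosen lambda is the largest whose cross-validated error is at most the minimum plus one SE, with SE = SD of the 10 fold errors/√10. Each data set was held fixed and only the folds were redrawn (8 data sets × 20 seeds per row).

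| n | columns | effects | typical list length | spread across seeds, median (range) | share of seeds giving the most common list | mean spread of predicted risk |
|---|---|---|---|---|---|---|
| 427 | 31 | full | 13 | 1.5 (1–2) | 66% | 0.031 |
| 427 | 48 | full | 16 | 2 (1–4) | 78% | 0.031 |
| 427 | 48 | halved | 11 | 5 (1–8) | 50% | 0.039 |
| 640 | 48 | full | 17 | 1.5 (1–5) | 68% | 0.026 |
| 107 | 48 | full | 9 | 2.5 (0–15) | 64% | 0.059 |
| 107 | 48 | halved | 5 | 4 (2–8) | 56% | 0.065 |

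Spread is the longest list minus the shortest within a data set. Predicted risk is from the LASSO fit, not the refitted model.

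**Common part of the list.** Lists along a LASSO path are nearly nested, so mean shortest over mean longest length approximates the share common to all seeds. With 427 patients, 48 columns and full effects this is 14.5/16.5 = 0.88, about 90%. With halved effects it is 8.8/13.1 = 0.67.

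**How often the list changed.** More than one list arose in every data set at 427 and 640. A separate run with full effects and 31 columns (12 data sets, 25 seeds) gave more than one list in 10 of 12 (83%), so a change is likely but not certain.

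**Another set of assumptions.** With 427 girls, 45 correlated candidates and 9 true effects (30 data sets, 60 seeds), the median spread was 4.5 around 8 selected, and the most common list came up in 59% of seeds.

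**Effect of averaging.** Averaging 10 repeats before applying the rule cut the median difference between runs to 0 in every row of the table. The maximum was 1, except 8 with halved effects at 107. Under the 45-candidate assumptions, averaging 20 repeats gave the same model size in 70% of data sets, with a largest spread of 4.

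**Fold noise against sampling noise.** A small check at 427 (4 data sets × 6 seeds per scenario, indicative only) compared selected lists by Jaccard overlap. It was 0.94–0.98 between seeds on the same data and 0.29–0.61 between independent samples.

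**The case against.** The strongest reply is that the premise rests on silence. Nowhere does the article say that only one partition is used, and seed, repeats and stratification are details that a journal article may leave to the full plan. Ten-fold cross-validation with the one-SE rule is also a conventional choice. This stands in part: single use is the natural reading of one described result, not an explicit statement, and the missing seed alone would be no finding. But the article does fix the step from a non-zero coefficient at that one lambda to a significant association, and a recorded seed would make the list reproducible without making it stable.

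A second reply is that fold noise is the smaller problem. That stands. The overlap figures suggest that sampling variation dominates, so selection frequencies over repeated folds on the same girls would make sample-specific factors look consistent.

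Two stronger readings should be resisted. A reader might infer that the article contradicts its own case for LASSO, since the Introduction credits it with stability because "LASSO can process all independent variables simultaneously". That stability is claimed relative to traditional regression, not as invariance to the folds, so there is no contradiction. A reader might also infer that the list will differ on every re-run. The most common list recurred in at least half of the seeds on average, so the supported word is could.

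Finally, the section also states: "Internal validation will be conducted using the 20% validation set samples". That conflicts with the preceding section, where the training data build the model. It is a separate fault, but the remedy must say where the folds are drawn.

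**Conclusion.** The point holds in a limited form. As described, one cross-validation result fixes lambda, and lambda alone fixes the list of factors and the model built on it. With 427 training patients, redrawing the folds moved the list length by a median of about 1.5 to 5 variables, and the most common list appeared in about 50 to 78% of seeds. With strong predictors the dependence is modest. It is larger with weak ones, and the documents give no ground for ruling those out.

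These sizes rest on the assumed effects, correlations and column count and on few simulated data sets, so they should be read as a range. The described conventional method is not wrong in itself; a more stable version is available at almost no cost. The inference that non-zero coefficients are significantly associated with depression is unsupported whichever partition is used.

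**What to change.** In the two sections on model building and internal validation:

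1. State that lambda is tuned in the training (development) data and not in the 20% validation set.
2. Repeat the 10-fold cross-validation over many random partitions stratified by depression status (for example 100). Average the cross-validated error and its standard error over the repeats, take the one-SE lambda from the averaged curve, and record the seed.
3. To say which factors the data support, draw bootstrap resamples of the girls, repeat the whole selection including tuning in each, and report how often each variable is selected. Frequencies across fold repeats alone show only fold noise and should not serve this purpose.
4. Describe variables with non-zero coefficients as selected predictors, not as significantly associated factors.

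The cost is a few sentences and a little more computing, with no new data. The averaging was tested with 10 and 20 repeats, not 100, and reduced the dependence on the folds without always removing it. The one uncomfortable consequence is that some factors may prove to be selected inconsistently, which readers need to know.
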